# Screening and patient-tailored care for emotional and cognitive problems compared to care as usual in patients discharged home after ischemic stroke (ECO-stroke): a protocol for a multicenter, patient-blinded, cluster randomized controlled trial

**DOI:** 10.1186/s12913-020-05902-2

**Published:** 2020-11-17

**Keywords:** Ischemic stroke, Screening, Cognitive and emotional problems, Randomized controlled trial, Cost-effectiveness, Process evaluation

## Abstract

**Background:**

Ischemic stroke patients with a good outcome in terms of motor functioning and communication are likely to be discharged home without further rehabilitation. A significant number of these patients experience cognitive and emotional problems resulting in lower quality of life and decreased participation in society. This paper presents the protocol of a study examining the clinical effectiveness, cost-effectiveness and implementation of an intervention focused on screening and patient-tailored care for cognitive and emotional problems as compared to usual care in patients discharged home after ischemic stroke.

**Methods / design:**

A multicenter, patient-blinded, cluster randomized controlled trial will be performed. Centers will be randomized (1:1) to the intervention group or the usual care group. Patients (> 18 years old) with a neurological confirmed diagnosis of ischemic stroke who can be discharged home without follow-up treatment at an outpatient rehabilitation clinic will be included. In the intervention group, patients will receive a short, individualized, semi-structured consultation by specialized nurses in addition to usual care. This consultation includes 1) screening for cognitive and emotional problems, 2) screening for restrictions in participation, 3) promotion of self-management strategies and 4) a decision tool for referral to rehabilitation services. The intervention will be performed approximately 6 weeks after the stroke at the neurology outpatient clinics and will take approximately 60 min. The control group will receive care as usual. Both groups will be followed-up at 6 weeks, 3 months and 12 months after stroke. The primary outcome will be the level of participation measured with the Restriction subscale of the Utrecht Scale for Evaluation of Rehabilitation on the level of Participation (USER-Participation-R) at 12 months. A cost-effectiveness analysis and process evaluation will be performed alongside.

**Discussion:**

This trial is the first to evaluate clinical effectiveness, cost-effectiveness and implementation of screening and patient-tailored care for cognitive and emotional problems compared to care as usual in patients discharged home after ischemic stroke. Potentially, this will improve the outcomes for patients with frequently occurring cognitive and emotional problems after stroke.

**Trial registration:**

Netherlands Trial Register: NL7295, registered 25 September 2018

## Background

### Introduction

Globally, stroke ranks third in leading causes of disability-adjusted life years [1]. Following stroke, many patients experience persistent deficits and reduced functional independence: over 30% of stroke survivors have persistent restrictions in participation after 4 years [2]. As a result, stroke causes a high social and economic burden [3].

After a major stroke, patients usually receive further rehabilitation treatment [2]. On the contrary, patients with a minor stroke who have a good outcome in terms of motor functioning and communication are mostly discharged home. A substantial number of these so called ‘walking and talking’ patients do not receive treatment at outpatient rehabilitation services [4]. However, many patients with minor stroke do experience cognitive and emotional problems [4–12].

Conventional clinical measures, such as a neurological examination, the National Institutes of Health Stroke Scale (NIHSS) or the Barthel Index (BI) (an instrument to measure a person’s functioning in activities of daily living), examine cognitive and emotional functioning at a rather global level. As a result, problems in the cognitive and emotional domains may be missed by health care professionals [5–13].

Cognitive problems are, nonetheless, the strongest predictor of return to work one-year post-stroke [6]. In addition, symptoms of anxiety and depression may hinder participation in society and return to work [7–10]. These problems can be a major contributor to a decreased participation, and a diminished quality of life [4, 14–16]. While national guidelines recommend screening and follow-up care for cognitive and emotional consequences after stroke, specific advice on the timing and guidance for follow-up care is lacking [2, 17, 18]. Therefore, the scientific board of neurologists in the Netherlands appointed this topic as a top priority for further research [19].

This trial aims to examine the clinical effectiveness, cost-effectiveness and implementation of an intervention focused on screening and patient-tailored care for cognitive and emotional problems as compared to usual care in patients discharged home after ischemic stroke.

### Study objectives

The study has three objectives: clinical effectiveness, cost-effectiveness and the implementation of the intervention.

### Primary objective

#### Clinical effectiveness

To determine the clinical effectiveness of an intervention focused on screening and patient-tailored care for cognitive and emotional problems as compared to usual care on patient-reported participation in patients with ischemic stroke discharged home without follow-up treatment at an outpatient rehabilitation clinic.

### Secondary objectives

#### Clinical effectiveness

To examine clinical effectiveness of the intervention compared to care as usual in terms of cognitive complaints, depressive and anxiety symptoms, quality of life, global health, physical disability, self-efficacy and patient satisfaction with stroke-care.

#### Cost-effectiveness

To examine the cost-effectiveness of the intervention compared to care as usual in terms of costs, effects and utilities from a societal perspective.

#### Process evaluation

To examine the implementation of the intervention from the perspectives of patients and professionals.

## Methods / design

### Study design

The ECO-stroke trial is a multicenter, patient-blinded, cluster randomized controlled trial. The Medical research Ethics Committees United (MEC-U) in Nieuwegein has approved that the current study is not subject to the Medical Research Involving Human Subjects Act (reference number: W18.169). Therefore, approval will be obtained from the local medical ethics committees of all participating hospitals. At time of submission of this manuscript, approval was obtained from the local medical ethics committees of the following hospitals: BovenIJ Ziekenhuis (reference: ECO-stroke), Noordwest Ziekenhuisgroep (reference number: L019–007), Ziekenhuis Amstelland (reference: ECO-stroke), Het Van Weel-Bethesda Ziekenhuis (reference: ECO-stroke), Tergooi (reference number: 19.24), Maasstad Ziekenhuis (L2019031), Zuyderland (reference: ECO-stroke), OLVG (reference number: WO 18.135) and Gelre ziekenhuizen (reference: ECO-stroke). The study is registered in the Netherlands Trial Register (NL7295) at 2018-09-25.

### Trial center eligibility and allocation

University and non-university hospitals in the Netherlands will be invited to participate in this study. All centers that intend to participate will be examined for their current stroke care by an online questionnaire and by interviews. Centers will be excluded from the study if one of the following criteria is met:
the current stroke care includes a screening for cognitive and emotional problems using validated screening instruments in the majority of stroke patients, within 3 months after stroke;the current stroke care includes long term follow-up (6 months or longer) with repeated cognitive and emotional assessments, with or without the use of validated screening instruments, in the majority of stroke patients.

After selection, the eligible centers will be randomized by an independent statistician in blocks of two in a 1:1 ratio to the intervention group or the usual care group using the web-based system Randomizer [20].

### Participants

A patient must meet all of the following criteria to be eligible to participate in this study:
clinical diagnosis of ischemic stroke as confirmed by a neurologist after history taking, neurological examination and CT-brain or MRI-brain;signs and symptoms resolve sufficiently to be discharged home directly without inpatient rehabilitation or follow-up treatment at an outpatient rehabilitation clinic.

Potential patients meeting any of the following criteria will be excluded:
age below 18 years;any serious comorbidity that 1) presumably interferes with the study outcomes (for example a psychiatric disorder for which supervision of a psychiatrist is needed), 2) has a progressive course (for example cancer, mild cognitive impairment or dementia) or 3) is associated with a patient’s life expectancy of less than 6 months;transient ischemic attack (TIA) defined as signs and symptoms that last less than 24 h and are not accompanied with ischemic lesions in the corresponding vascular territory on CT- or MRI-scan;hemorrhagic stroke;unable to understand questionnaires based on clinical judgement, for example due to insufficient command of Dutch or aphasia;legally incompetent on the basis of clinical judgment;no informed consent.

### Recruitment and consent

Within 4 weeks after the ischemic stroke, the patient will be asked to participate by his/her treating health care professional either during admission, at the outpatient neurology clinics, at the emergency room or at home by phone. All patients are free to choose whether or not to participate. If the patient agrees to take part in the study, the informed consent form will be signed.

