### Blinding

Before and during the study, patients will not be informed about the treatment allocation of their hospital. Therefore, patients will be blinded during the study period. After the study patients will be informed whether or not the intervention was received. Due to the nature of the intervention and due to the cluster randomization, the researchers and the treating health care professionals will not be blinded. However, all measurements, except for the secondary outcome measurement modified Rankin Scale (mRS), will be completed by the patients without assistance of the researchers or treating health care professionals. As such, outcome measurements will be administered in a blinded manner.

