### Statistical analysis

#### Clinical effectiveness

Descriptive statistics will be used to describe baseline data and outcomes. Normal Q-Q Plots and the Shapiro-Wilk test will be performed to test for normality. In normally distributed continuous variables, means and standard deviations will be used. Non-normally distributed variables and ordinal variables will be expressed by medians and interquartile ranges. Categorical variables will be described by counts and percentages. Missing data will be handled by multiple imputations. Two-sided 95% confidence intervals (CI) will express the statistical uncertainty; a two-sided *p*-value < 0.05 will be considered statistically significant. Multiple testing will not be corrected for. An intention-to-treat principle will be applied to the statistical analyses.

We will perform the main analysis of the primary outcome on the change (delta) USER-Participation-R scores between 6 weeks and 12 months and a sensitivity analysis on the observed USER-Participation-R scores at 12 months. We will use a linear mixed effects model with center as a random effect and treatment arm as a fixed effect for both analyses. In addition, we will analyze the three repeated measurements (6 weeks, 3 months and 12 months) of USER-Participation-R scores using a single linear mixed effects model with nested random effects for patients within centers and treatment arm as a fixed effect.

For the continuous secondary outcome parameters (CLCE-24, HADS, PROMIS-10 and GSES) we will use the same statistical modelling approach as described above.

The continuous secondary outcome parameter SASC-19 will be analyzed using an unpaired t-test.

With regard to the ordinal scores on the mRS we will calculate the within-group median change scores as the 50th percentile of all individual differences (change from baseline to 1-year outcome assessment). Point estimate and 95% CI of the median difference in change scores between treatment groups will be calculated using the Hedges-Lehmann method [36]. Between-group difference in change scores will be analyzed using the Mann-Whitney test.

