The strengths of the study are the following. First, this study will examine the intervention in a large sample of patients in a randomized manner, which will minimize the chances of bias. Second, the local health care professionals will execute the study intervention, therewith reflecting actual clinical practice and increasing external validity as well as facilitating implementation after the trial. Although this might result in variation in conducting the intervention, thereby introducing bias, we consider this as strength since this reflects the future practice, resulting in stronger generalizability of the findings. Third, the intervention was developed by the collaboration of a multidisciplinary team and aims to further improve the collaboration between health care professionals at the neurology department and the rehabilitation department. Fourth, this study examines an important topic as prioritized by previous patient evaluations and evaluates its effectiveness based on Patient Reported Outcome Measures (PROMs) [45, 46]. Fifth, the intervention will be analyzed from both a clinical and economic perspective, and the implementation of the intervention will also be examined.

The following limitations apply to this study. First, since the intervention is a consultation, blinding of the health care professionals is not possible. However, the patient will not be informed whether or not the intervention was supplied; since most outcomes are patient-reported measurements, we expect to minimize the influence of health care professionals being aware of the allocation. Second, a cluster randomization is methodologically weaker than a patient-level randomization. However, a patient-level randomization was considered unfeasible since most hospitals have only one health care professional occupied with stroke care at the outpatient clinics. Besides, if a hospital would have two or more health care professionals providing the stroke care, contamination from the intervention-trained nurse to the untrained nurse would be likely.

In conclusion, this trial will investigate the clinical effectiveness, cost-effectiveness and implementation of active screening and patient-tailored care for cognitive and emotional problems compared to care as usual in patients discharged home after ischemic stroke.

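### Staff who know their centre's allocation recruit the patients, and the stated models, with treatment arm as the only named fixed effect, correct only part of the imbalance this could cause.

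*Protocol article*

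**What the plan says.** - **Allocation** (Trial center eligibility and allocation): "After selection, the eligible centers will be randomized by an independent statistician in blocks of two in a 1:1 ratio".
- **Recruitment** (Recruitment and consent): within 4 weeks of the stroke, "the patient will be asked to participate by his/her treating health care professional".
- **Blinding**: "the researchers and the treating health care professionals will not be blinded". On the patient side, "Before and during the study, patients will not be informed about the treatment allocation of their hospital".
- **Eligibility** (Participants): some criteria need judgement. Examples are "signs and symptoms resolve sufficiently to be discharged home directly", comorbidity that "presumably interferes with the study outcomes", and ability to understand the questionnaires.
- **Analysis** (Statistical analysis, Clinical effectiveness): the main analysis is the T1-to-T3 change in USER-Participation-R, and the sensitivity analysis is the 12-month score. Both use a linear mixed model "with center as a random effect and treatment arm as a fixed effect for both analyses". A third model takes all three time points, again naming only arm as a fixed effect. CLCE-24, HADS, PROMIS-10 and GSES follow the same approach.
- **Data available** (Data collection and Table 1): age, sex, education, admission NIHSS, discharge mRS and the T1 questionnaires are all recorded.
- **Discussion**: the strengths paragraph says the intervention is examined "in a randomized manner, which will minimize the chances of bias". The limitations concede that cluster randomization is the weaker design. They treat unblinded staff only as a possible influence on outcome reporting.

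**The concern.** When whole centres are randomized and patients are recruited afterwards by people who know the arm, randomization balances centres, and with six per arm only roughly. It does not govern which patients enter. Staff in an intervention centre may be readier to invite a patient who seems likely to gain from the consultation, and staff in a usual-care centre have no such reason. If that happens, the arms differ in prognosis before the intervention starts, and part of the estimated effect is recruitment. The bias can go in either direction. The stated models include no patient characteristic that could absorb the measured part of such a difference.

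**Working it through.** **1. Sequence.** No single sentence says that recruitment follows known allocation. It follows from three places: centres are randomized once selected, nurses in intervention centres are trained before delivering the consultation, and treating staff are stated to be unblinded. The article describes no independent recruiter and no allocation-blind eligibility check.

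**2. The plan's own figure.** Inputs from Sample size: 6 centres per arm, 36 patients each (216 per arm), effect 0.35 SD, intracluster correlation 0.01, t-test on the number of clusters.
- Design effect: 1 + (36 − 1) × 0.01 = 1.35
- SE: √(2 × 1.35 / 216) = 0.112 SD
- Power, noncentral t with 2 × (6 − 1) = 10 df: 80.5%, against a stated 81%. The sample size is not in question.

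**3. Bias if selection is on T1 status.** Let D be the between-arm T1 difference caused by recruitment, in SD units, and rho the T1–T3 correlation. Neither is in the documents, so both are assumed. The 12-month SE is 0.112; it is multiplied by √(2(1 − rho)) for change and by √(1 − rho²) for a T1-adjusted analysis.
- 12-month score: bias = rho × D
- Change score: bias = (rho − 1) × D
- T1-adjusted: bias = 0

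With D = 0.2 and rho = 0.5, the 12-month bias is 0.5 × 0.2 = +0.10 SD and the change bias is (0.5 − 1) × 0.2 = −0.10 SD. The change SE factor is √1 = 1, so each bias is 0.10 / 0.112 = 0.89 SE. Relative to the target, 0.10 / 0.35 = 29%.

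**4. Bias if the shift is constant over time.** The 12-month bias is D, the change bias is 0, and the T1-adjusted bias is (1 − rho) × D.

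| Analysis | Type I error, selection on T1 (D 0.2, rho 0.5) | Range (D 0.1–0.3, rho 0.3–0.8) | Type I error, constant shift (D 0.2, rho 0.5) |
|---|---|---|---|
| Change | 12.8% | 5.8%–30% | 5.0% |
| 12-month score | 12.8% | 5.7%–49% | 36.6% |
| T1-adjusted | 5.0% | 5.0% | 15.5% |

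**5. Bias through another prognostic factor.** The 12-month bias is imbalance × slope on T3. The change bias is imbalance × (slope on T3 − slope on T1). With an assumed imbalance of 0.2 SD and T3 slope of 0.4, the 12-month bias is 0.08 SD (0.08 / 0.35 = 23% of the target). For change it is 0.2 × (0.4 − 0.3) = 0.02 SD (6%) if the T1 slope is 0.3, zero if the slopes are equal, and 0.08 SD only if the factor is unrelated to T1 participation.

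**6. Precision.** If the covariates explained 20% of outcome variance (assumed, within and between centres alike), the SE would be √(2 × 0.8 × 1.35 / 216) = 0.100 and power 88%.

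**The case against.** A reader might infer that differential recruitment goes wholly uncorrected. The documents do not support that: the main response is a change score, which subtracts any constant participation gap exactly. A reader might also carry the 23% in step 5 over to the main analysis, but it belongs to the 12-month sensitivity analysis.

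Other points on the plan's side:
- **Patients are not told the allocation.** This limits differential consent. It does not affect whom staff approach.
- **The opportunity is limited.** Discharge home without rehabilitation is a care decision that actually takes place, and recruiters lack the T1 scores because they recruit before 6 weeks. This narrows the room for selection without closing it. That intervention staff would select differently is a risk, not an observed fact.
- **Covariates cannot remove selection on clinical impression.** This stands. The covariates proposed here capture suspected cognitive or emotional problems only indirectly, mainly through the T1 score. In a population selected for good recovery, NIHSS and mRS may vary little, so the 20% variance explained may not be reached.
- **Covariates may be left to the analysis plan.** That would excuse silence. The article instead writes the models out and names one fixed effect, so the point concerns a stated model.
- **The Discussion already calls the cluster design weaker.** It does, but it does not name recruitment bias.

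**Conclusion.** The concern holds in a limited form. Allocation-aware staff recruit on partly judgement-based criteria, and the stated models handle only one kind of resulting imbalance: a constant participation gap, and that only in the main change analysis. Regression to the mean and case-mix differences that affect recovery remain there, and the 12-month analysis has no baseline protection. Under selection on T1 status, the main and sensitivity analyses would be biased in opposite directions, so agreement between them could not be taken for granted.

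The size is unknown. The ±0.10 SD and roughly 13% type I error rest on assumed D = 0.2 SD and rho = 0.5. No single model is safe under every mechanism: T1 adjustment is unbiased when selection acts through T1 status, and the change score when the shift is constant. That supports prespecifying an adjusted model and keeping the unadjusted change analysis beside it. It should be changed, but the documents do not show that the primary result will be biased.

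**What to change.** 1. In the Clinical effectiveness part of Statistical analysis, prespecify the T1 score, age, sex, education, admission NIHSS and discharge mRS as patient-level fixed effects in the USER-Participation-R mixed models and the continuous secondary models. Keep centre as a random effect, and keep the unadjusted models as sensitivity analyses.
2. In the three-time-point model T1 is itself a response. If it becomes a covariate there, only T2 and T3 should remain as responses.
3. For CLCE-24, note that T1 is nurse-administered in one arm and self-reported in the other, so its T1 score is not a like-for-like baseline.
4. State that adjustment removes measured imbalance only.
5. Report numbers screened and included by arm from the screening log. The Process evaluation section does not say that the log holds age, sex or reasons for non-inclusion, so a comparison on those depends on what was recorded.
6. In the Discussion, name recruitment bias as a limitation and soften the claim that randomization minimizes bias.

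The cost is wording. The covariates are already collected, they use a few patient-level degrees of freedom and none at centre level, and no visit or patient is added. Any power gain is a side benefit that depends on the variance explained. The list should be fixed before outcome data are examined, because covariates chosen after an imbalance is seen carry less weight.
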